### Sample size

The primary evaluation criterion is the change over 2 weeks in performance on the SA task. Performance is measured by the percentage of correct responses. The trial will be considered as positive if performances after left-anodal or right-cathodal tDCS are shown to be significantly superior to sham stimulation. The sample size is based on the results of a preliminary study comparing sham stimulation to left-anodal and right-cathodal stimulation in 12 patients [45]. In our pre-therapeutic study, the mean difference in performance improvement between sham and both anodal and cathodal stimulation was about 15% with a standard deviation of 16% and an effect size of 1.464. The difference in mean change between sham stimulation and each of the two other groups is then expected to be 15% of correct responses. The inclusion of 20 patients in each group will provide statistical power of 80%.

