The purpose of this article is to present a clinical protocol (PHRC “STIM-SD”*)* implementing a multi-day tDCS regime in a large population of patients with SD (*n* = 60) specifically targeting the left ATL (with anodal stimulation) or the right ATL (with cathodal stimulation) to provide evidence for potential therapeutic effects and brain plasticity outlasting the duration of the treatment. This intervention builds on a previous pre-therapeutic double-blind, sham-controlled study by our team using a single tDCS session applied to the left and right ATL in patients with SD [45]. This approach allowed the comparison of left anodal (excitatory) to right cathodal (inhibitory) tDCS stimulation and showed that a single session of both left anodal and right cathodal tDCS resulted in transient but highly significant intra-semantic effects [45]. The goals of the present study include the evaluation of the potential therapeutic efficacy of periodical sessions of tDCS over the ATL during 10 days in language/semantic performance in patients with SD, the assessment of the time course of potential improvements, the exploration of potential effects on brain plasticity using functional connectivity measures (resting-state functional magnetic resonance imaging (fMRI)) and cortical metabolism (fluorodeoxyglucose positron emission tomography (FDG-PET)), the identification of the most efficient stimulation modality (left-anodal versus right-cathodal) and the identification of biomarkers such as ATL atrophy levels, which could be individually indicative of an efficient tDCS impact.

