### Data analyses

We will accept a significance level of 5% (*p* < 0.05) corrected for multiple comparisons when needed. To assess our primary endpoint criterion, i.e., performance changes on the SA task, outcomes at baseline and at the 2-week time point will be compared using two-way analysis of variance with “time” (baseline, 2 weeks post-stimulation) and “group” (anodal, cathodal, sham) as factors. Since two comparisons will be made (sham versus left-anodal and sham versus right-cathodal tDCS) Dunnett’s two-tailed *t* test will be used to handle multiple comparisons. In the case that the data do not meet the normal distribution assumption, the non-parametric Mann-Whitney test will be used to compare performance improvements between the sham versus left-anodal and between the sham versus right-cathodal groups.

To assess the time course of potential improvements and test if such differ between the treatment groups, linear mixed models will be used with “time” (the four time points), “group” (anodal, cathodal and sham) and group-by-time interactions as fixed effects. The Benjamini and Hochberg method will be used for controlling for false discovery rate.

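### The stated effect size of 1.464 does not follow from 15 points and SD 16 (0.94), and the stated 80% power fits an unadjusted comparison, not the planned Dunnett test (about 76% per comparison, about 88% for at least one)

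*Protocol article*

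**What the plan says.** The Sample size section takes its inputs from a preliminary study of sham, left-anodal and right-cathodal stimulation in 12 patients. It reports that the mean difference in improvement between sham and both active conditions "was about 15% with a standard deviation of 16% and an effect size of 1.464". It then plans on a 15-point difference in mean change between sham and each active group, and concludes: "The inclusion of 20 patients in each group will provide statistical power of 80" per cent. The same section calls the trial positive if either active arm is significantly superior to sham.

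The Data analyses section sets the overall level: "We will accept a significance level of 5" per cent, corrected for multiple comparisons when needed. For the primary endpoint it states that "two comparisons will be made (sham versus left-anodal and sham versus right-cathodal tDCS"), and that Dunnett's "two-tailed *t* test will be used to handle multiple comparisons". If normality fails, "the non-parametric Mann-Whitney test will be used to compare performance improvements" between each active group and sham.

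The article does not say what kind of effect size 1.464 is, which test and level the 80% refers to, or whether the 80% is per comparison or for the either-arm rule.

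**The concern.** Two things in the sample-size paragraph do not fit together.

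First, three figures stand in one sentence, and the third is not the ratio of the first two. A reader who takes 1.464 as the design effect would think the trial very heavily powered. A reader who takes 15 and 16 would think it moderately powered.

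Second, the power is stated without a test, while the primary analysis splits the 5% error over two comparisons. That adjustment costs power for each comparison, and the stated 80% does not appear to include it.

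At stake is how a null result for one arm would be read. The article also wants to identify the more efficient modality, so the power of each comparison with sham matters as well as the power to show at least one success.

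**Working it through.** **Inputs.** From Sample size: difference 15 points, SD 16 points, effect size 1.464, n = 20 per group, power 80%, success if either active arm beats sham. From Data analyses: two-sided 5%, two comparisons with sham, Dunnett. Assumption, not stated in the article: 16% is the between-patient SD of the change score in each parallel group. All figures take 20 evaluable patients per group.

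**1. Effect size.**
- 15/16 = 0.9375.
- An effect of 1.464 needs an SD of 15/1.464 = 10.2, or a difference of 1.464 × 16 = 23.4 points. The word about in front of 15% cannot cover that gap.
- A paired effect size could give 1.464. If 16 is the SD within each condition, the SD of the within-patient difference is 16 × √(2(1 − r)). Setting this to 10.25 gives 1 − r = 10.25²/(2 × 16²) = 0.205, so r is about 0.79. The article states no such correlation.

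**2. Reproducing the stated figure.** For an unadjusted two-sided 5% comparison of two groups with d = 0.9375:
- The normal approximation needs 18 per group; the t test needs 19 (80.3%).
- At n = 20 the noncentrality is 0.9375 × √(20/2) = 2.965. Power is 82.4% by t test (38 df), 84.2% by normal approximation, and 80.5% by Mann-Whitney with an assumed relative efficiency of 0.955.

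So 20 per group and 80% are reproduced, but only with no allowance for two comparisons.

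**3. Could 1.464 be the basis?** At n = 20 the noncentrality would be 1.464 × √10 = 4.63. Power would be 99.5% by unadjusted t test and 99.0% per Dunnett comparison. About 10 per group would already give 82% with Dunnett. It cannot be the basis of 80% at 20 per group.

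**4. The planned test.** Two-tailed Dunnett, two comparisons, correlation 0.5, 3 × (20 − 1) = 57 df:
- Critical value 2.268.
- Power per comparison = P(noncentral t with 57 df and noncentrality 2.965 exceeds 2.268) = 75.5%; simulation of 1,000,000 trials gives 75.6%.

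| n per group | Power per Dunnett comparison |
|---|---|
| 20 | 75.5% |
| 21 | 77.8% |
| 22 | 79.9% |
| 23 | 81.9% |

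**5. The either-arm rule at n = 20 (simulation).**

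| True situation | At least one arm shown superior | Both shown superior |
|---|---|---|
| Both arms gain 15 points over sham | 88.1% | 63.1% |
| Only one arm gains 15 points, the other 0 | 75.6% | not applicable |

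Neither reading of the planned analysis gives 80%: it is about 76% or about 88%.

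**The case against.** The strongest reply is that the 80% is not labelled. The article declares success if either arm beats sham, and for that rule the Dunnett test has about 88% power when both arms work as assumed. On that reading the trial is not short of power. This stands in part. A reader might infer that the trial is underpowered for its declared goal, and the document does not support that. But the 88% requires both arms to gain 15 points; if only one does, the figure falls back to about 76%. The section also frames the expected difference for each of the two active groups separately, which points towards a per-comparison figure without settling it.

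A second reply is that 1.464 may be a correct pilot result. The effect size is undefined, and a paired one from the 12-patient study need not equal 15/16. This also stands. A reader might infer that 1.464 is simply an error, but that cannot be shown from the article. What can be shown is that it is unexplained, does not follow from the figures beside it as a between-group quantity, and did not produce the sample size. The same ambiguity touches the 16%: if it is the SD of within-patient differences, 15/16 is not a parallel-group effect either, and both the 80% and the 76% become conditional.

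Third, the gap is small: 80 − 75.5 = 4.5 points, or 2 to 3 patients per group. That is right, and it limits the weight of the point.

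Two further criticisms might be inferred and are not made here. The article mentions no allowance for dropout, but a condensed article may leave that to the full protocol. And the article says a single session "resulted in transient but highly significant intra-semantic effects", which could be used to argue that 15 points is too optimistic two weeks after treatment. That is a judgement about plausibility, with the pilot basis openly disclosed, and ten sessions may do more than one.

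**Conclusion.** The concern holds in a limited form: the power statement does not describe the planned primary test, and the effect size printed beside it is unusable for this parallel-group design as it stands. The sample size itself is close to what the inputs 15 and 16 require for one unadjusted comparison. The results rest on 16% being the between-patient SD of change, on normally distributed changes with equal SDs, and on 20 evaluable patients in each group. This is a correction to a stated figure; it gives no reason to change the design.

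**What to change.** In the Sample size section:

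1. Remove 1.464, or define it as a pilot effect size (for example a paired one, if that is what it is) and say that it was not used for the parallel-group calculation.
2. State that 16% is the SD of the change score assumed within each parallel group, so that the design effect is 15/16 = 0.94. If the 16% is something else, say what it is and redo the calculation.
3. Replace the 80% with: *With 20 evaluable patients per group, power is about 76% for each two-sided Dunnett comparison with sham, and about 88% to show at least one active arm superior if both are equally effective.* Adding that the latter falls to about 76% if only one arm works would make it complete.

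The cost is wording only. Arms, endpoint, test, success rule and number of patients stay as they are. The one drawback is that the per-comparison figure is slightly less favourable than the one now printed. If the sponsor wanted at least 80% for each comparison, these inputs would require 23 per group, but the correction does not depend on that.

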## Discussion

Language disorders in frontotemporal lobar degeneration, and particularly in SD, are a disabling feature representing an important medical problem. They are also a relevant issue for public health because most patients have symptoms prior to retirement causing substantial health costs. Given this context our project bears major importance because it could potentially provide evidence for the validity of a novel therapy strategy improving language/semantic capacities while diminishing the functional handicap and, eventually, healthcare expenditure.

The STIM-SD protocol proposes the first large-scale exploration of tDCS as a potential therapy for language/semantic impairment in SD for which no treatment is currently available. Contrary to most of the studies using transcranial brain stimulation in neurodegenerative diseases affecting language [43, 44, 67, 68], our study targets sites that have been selected based on the localization of anatomical damage and related contralateral regions to optimize language and semantic recovery.

We apply a double-blind, sham-controlled design in which the investigators and the patients are blinded to the type of stimulation used, reducing any source of potential bias. This design will also enable a comparison between two different stimulation approaches (left-anodal versus right-cathodal) and will contribute to identifying the most beneficial strategy. To our knowledge, not a single study applying tDCS to improve cognitive deficits in neurodegenerative diseases has employed supportive neuroimaging (PET, fMRI), and only one study has used neurophysiological measures (EEG) [69] to explore stimulation impact on relevant brain networks or demonstrate neuroplasticity effects. In the present study, we will generate both language/semantic data and a set of neuroimaging and resting-state EEG measures, which will allow us to study the impact of tDCS on language networks and neuroplasticity, to understand if this potential impact also subtends language/semantic improvements, and to better understand tDCS mechanisms.

In addition, baseline structural data (3D-T1 cortical thickness, DTI fiber tract analyses) and individualized models of tDCS current magnitude and distribution will be fundamental in understanding which anatomical features of our cohort most influence treatment efficacy, how the amount and spreading of electric current in the brain will impact individual clinical outcomes and possibly define a profile of patients that in the future would most benefit from tDCS.

Within neurodegenerative diseases specifically affecting language, SD is the most frequent variant of primary progressive aphasia [2], which contributes to the feasibility of the project in terms of patient recruitment. In the same vein, our National Reference Center for Rare or Early Onset Dementias provides a unique opportunity to recruit a large and homogeneous cohort of patients with SD. The active patient files on patients with early-stage SD in the three recruiting centers contained more than 20 patients with SD per year in 2013, 2014 and 2015. This shows that the total number of 60 patients with SD can be reached in the current project.

A potential tDCS treatment would be easily applicable, inexpensive and renewable when therapeutic effects disappear due to disease evolution. Significant effects of repetitive tDCS on language/semantics would also open an avenue for future tDCS trials targeting language non-related cortical regions such as areas subtending episodic memory, which is damaged, for example, in Alzheimer’s disease. More generally, the protocol might improve the understanding of neuroplasticity and its modulation through inhibitory and/or excitatory tDCS-driven cortical impact, while providing a rationale for appropriate stimulation modalities and for identifying brain regions likely to demonstrate relevant plasticity. Such insights could prove important for both tDCS and TMS trials, and their combination with behavioral language rehabilitation strategies, which might further enhance plasticity-related modulation.

## Conclusions

The aim of the STIM-SD protocol is to implement a novel therapeutic tDCS approach to language/semantic deficits in patients with SD for whom no treatment is available. If found to be efficient, this strategy could be regularly implemented, as it is easily applicable and low-cost. Moreover, larger trials could be extended to other neurodegenerative diseases to check for efficiency in language and other cognitive functions.

### Trial status

The protocol version number is P160937J first published in ClinicalTrials.gov on 29 March 2018. Patient recruitment began in June 2018. Sixteen patients have been screened for participation between June 2018 and March 2019. Of these, 13 patients were included in the study and randomized. Seven of those patients have already completed their participation in the study with 4-month follow up. Among the three patients screened but not included, two patients did not meet all the inclusion criteria while another was not able to undergo the planned neuroimaging examinations. Five healthy participants were also included in the protocol. Recruitment is expected to be completed by June 2021.

## Data Availability

Not applicable. No data is available at this point because authors are still in the process of gathering such.
